### Sample size

A sample size calculation was performed based on an objective measure of physical activity level, i.e. counts per min, derived from an accelerometer. A total of 160 participants (80 patients per group) will be required to detect a 20% between-group difference in physical activity levels (mean difference between groups of 59.2 counts per min, a standard deviation of 111.6 counts per min) with a power of 0.80, alpha of 0.05 accounting for a 15% loss to follow-up. The counts per min parameters used in the sample size calculation are from a previous study conducted with a similar population [22]. The total of 160 participants is enough to detect a between-group difference of 1 point (standard deviation (SD) = 1.84) in the numerical pain rating scale and of 4 points (SD = 4.9) in the Roland Morris Disability Questionnaire (RMDQ) with a power of 80%, an alpha of 0.05 and 15% dropout as reported in a previous trial with this population [23].

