#### Primary outcomes

Physical activity – counts per min is the main objective measure of physical activity and will be measured with the Actigraph GT3X (ActiGraph, LLC, Pensacola, FL, USA). The Actigraph GT3X is a non-invasive, small (4.6 × 3.3 × 1.5 cm) triaxial accelerometer worn above the right hip for seven consecutive days during waking hours. Acceleration data will be sampled at 30 Hz and analysed at 60-s epochs. A complete data set for each patient will be defined as having at least 10 h/day of monitored wear over at least 5 days [34]. Non-wear periods will be defined as time intervals of at least 60 consecutives min of zero counts, with an activity interruption allowance of 0 to 100 counts/min lasting a maximum of two consecutive days [35]. These parameters have been used in previous studies from our group [22, 36]. Counts per min will be calculated by dividing the sum of activity counts of the vertical axis by the number of valid daysDisability – the Roland Morris Disability Questionnaire (RMDQ) [37] will be used to measure disability. The RMDQ consists of 24 yes-or-no questions with total scores ranging from 0 to 24 and higher scores indicating greater disabilityPain intensity – Numerical Rating Scale for pain assessment (NRS) will be used to measure pain intensity. The NRS evaluates the pain intensity in the last week through an 11-point-scale from 0 to 10 with higher scores indicating greater pain intensities

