#### Secondary outcomes

Other objective measures of physical activity, such as time spent in light and moderate-vigorous physical activity, number of steps and time spent in sedentary behaviour, will be considered secondary outcomes. These data will be collected with the same procedure reported for counts per min. Sedentary time will be defined as values less than 100 count/min, light physical activity will be defined as values between 100 and 2019 counts/min and moderate-vigorous physical activity will be defined as values greater than 2020 counts/min [34]Self-reported physical activity level will be measured with the Baecke Habitual Physical Activity Questionnaire [22]. This questionnaire consists of 16 items covering three dimensions: leisure-time and locomotive physical activities; leisure-time physical exercises; and occupational physical activities. The total score ranges from 3 to 15, with higher scores indicating higher physical activity levelsSelf-reported sedentary behaviour will be measured with questions about the time spent in sedentary behaviour across five different domains in a usual weekday [38]: workplace, commuting, school/university, watching TV, and computer use. Before quantifying the time spent in each sedentary activity, the participants will be asked if they are exposed, or not, to each behaviour. We will use the sum of the domains as well as the time spent in each sedentary behaviourDepression will be assessed with The Center for Epidemiological Studies – Depression (CES-D) scale [39]. The CES-D scale assesses the frequency of depression symptoms in the last week with 20 questions. Total scores range from 0 to 60 and higher scores indicate higher depression levelsQuality of life will be assessed using the EuroQol Visual Analogue Scale (EQ-VAS) [40]. In the EQ-VAS, respondents report their perceived health status with a grade ranging from 0 (the worst possible health status) to 100 (the best health status)The Pain Self-Efficacy Questionnaire (PSEQ) [41] will be used to assess pain self-efficacy. The PSEQ contains 10 items with scores ranging from 0 to 6. Final scores range from 0 to 60 with higher scores indicating more confidence to perform an activity despite the painWeight-related outcomes – Body Mass Index and waist-to-hip circumference will be used to measure weight-related outcomes. Body Mass Index will be calculated based on weight and height measured by a digital scale and an stadiometer and waist and hip circumference using an anthropometric measuring tape. Waist circumference will be measured midway between the 10th rib and the top of the iliac crest and hip circumference as the widest part over the buttocks to the nearest 0.5 cm

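### The scoring rule for the physical activity primary outcome gives counts per day, not the counts per minute that the article names and sizes the trial on

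*Protocol article*

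**What the plan says.** The Primary outcomes section of the protocol article states that "counts per min is the main objective measure of physical activity and will be measured with the Actigraph GT3X". The device is "worn above the right hip for seven consecutive days during waking hours", and a complete record needs "at least 10 h/day of monitored wear over at least 5 days". The scoring rule then reads: "Counts per min will be calculated by dividing the sum of activity counts of the vertical axis by the number of valid" days.

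The Sample size section rests on the same named quantity: "A sample size calculation was performed based on an objective measure of physical activity level, i.e. counts per min, derived from an accelerometer". The inputs are a "mean difference between groups of 59.2 counts per min, a standard deviation of 111.6 counts per min", and the aim is to "detect a 20% between-group difference in physical activity levels".

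The article gives no other formula for this outcome and no conversion from a daily total to a rate. The linear mixed model in the Data analysis section lists fixed effects for group, time and their interaction, so wear time is not taken up there either.

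**The concern.** A count total divided by a number of days has the unit counts per day. A rate per minute needs minutes in the denominator. The article does not leave the scoring to another document. It states a rule, and that rule cannot give the quantity it names.

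If every participant wore the device for the same time on each valid day, the two quantities would differ by a constant and little would follow. Wear is not fixed, however: the article sets a floor of 10 h and asks for wear during waking hours. Applied as written, the score mixes how intensely a person moved with how long the device was on, and it does so differently between people and between visits. Anyone scoring or replicating from the published text would analyse a different variable from the one the trial was sized on.

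**Working it through.** **Inputs.** Difference 59.2 and SD 111.6 counts per minute, a 20% difference, power 0.80, alpha 0.05, 15% loss and 80 per group (Sample size). Minimum wear of 10 h on at least 5 days, and the scoring rule (Primary outcomes). All wear times other than the 10 h minimum are my assumptions.

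**1. The plan's own figure.** With a two-sided alpha (sidedness is not stated), n per arm = 2 × (1.960 + 0.842)² × (111.6/59.2)² = 2 × 7.85 × 3.554 = 55.8, so 56. Allowing for 15% loss, 56/0.85 = 65.9, so 66 per arm and 132 in total. The stated 160 is not reproduced. It errs on the safe side, and the present point does not depend on it. With 80 × 0.85 = 68 evaluable per arm, power is about 87%.

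**2. Units.** Let C be the summed vertical-axis counts, D the number of valid days and W the total valid wear minutes.
- Rule as written: C/D, in counts per day.
- Quantity named and powered: C/W, in counts per minute.
- Link: C/D = (C/W) × (W/D), the rate multiplied by the mean wear minutes per valid day.

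The written score therefore moves in proportion to wear when the rate is held fixed.

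**3. Size of the wear effect.** Implied mean: 59.2/0.20 = 296 counts per minute. For a participant at that rate:

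| Wear per valid day (12 h and 14 h assumed) | Score as written, 296 × minutes | Target difference on that scale, 59.2 × minutes | One extra hour (296 × 60 = 17,760) as share of target |
|---|---|---|---|
| 10 h (600 min) | 177,600 | 35,520 | 50% |
| 12 h (720 min) | 213,120 | 42,624 | 42% |
| 14 h (840 min) | 248,640 | 49,728 | 36% |

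From 10 h to 12 h the score rises by 213,120/177,600 − 1 = 20% with no change in intensity. This takes the extra minutes to be of average intensity. If they carried no counts, the score would not move at all.

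**4. Noise, with no imbalance between arms.** Assume mean wear of 13 or 14 h (m minutes), a between-person SD of 1 to 2 h (s minutes), and wear independent of intensity. The variance of the written score is then 111.6²m² + 296²s² + 111.6²s², and the target difference is 59.2m. With 68 per arm:
- 13 h, SD 1 h: score SD 89,093, power 0.856.
- 13 h, SD 2 h: score SD 94,965, power 0.809.
- 14 h, SD 1 h: score SD 95,646, power 0.858.
- 14 h, SD 2 h: score SD 101,138, power 0.818.

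Power falls from about 87% to between 81% and 86%, still above the planned 80%.

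**The case against.** The best reply is that the intention is plain. The outcome is named counts per minute, the data are analysed in 60-second epochs so that each epoch value is already a count per minute, and the sizing figures come from an earlier study whose accelerometer settings this trial says it shares. On this view, days is a slip for minutes, or the sentence condenses an average of daily rates over valid days. A score near 200,000 against a planning mean of 296 would be noticed at once. Much of this stands: a slip is the likeliest explanation. But the sentence speaks of a sum of activity counts, not of daily rates, and nothing else in the article corrects it.

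A reader might infer more than the article supports:

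- **A large scale error.** The written score is 600 to 840 times the planning value at 10 to 14 h of wear. A constant multiplier changes neither a test nor its power. Only the variation in wear matters.
- **Bias driven by coaching.** Feedback in the intervention arm comes from the wrist-worn Fitbit Flex. The outcome comes from a separate hip-worn Actigraph. Controls get a sham Fitbit with the same information about the device, matched weekly contact and blinded outcome assessors. Nothing says that coaching addresses Actigraph wear, so a difference in wear between arms is possible but not shown.
- **The same fault in the secondary outcomes.** The article says "These data will be collected with the same procedure reported for counts per min". That describes collection, not the division. Minutes and steps per valid day are dimensionally sound, and a percentage of wear time or a wear-time covariate would be an analysis preference.
- **A separate numerator error.** The rule does not say that counts are restricted to valid days, but the validity criteria come just before it and a denominator of valid days implies the restriction. This is a clarification for the same sentence.

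**Conclusion.** The point holds in a narrow form: the published rule for the physical activity primary outcome is wrong as written. It yields counts per day, which contradicts both the named unit and the unit of the sample size inputs.

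Applied literally, the score would depend on wear time, by as much as the full 20% target between 10 h and 12 h at equal intensity. That figure rests on assumed wear and on extra minutes of average intensity. The loss of power under the assumed spread of wear is modest, and bias would need a difference in Actigraph wear between arms that the article does not show. The sample size inputs are already in counts per minute and do not change. Pain and disability, the other two primary outcomes, are unaffected. The correction should still be made before analysis, because the sentence defines the outcome on which the first sample size calculation rests.

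**What to change.** Replace the scoring sentence with one to this effect: counts per minute are the sum of vertical-axis counts over valid wear minutes on valid days, divided by the total valid wear minutes on those days. This also settles the restriction of the numerator to valid days. Then confirm that the scoring script does exactly this. If the script instead averages daily rates over valid days, that too is in counts per minute, but it weights days equally and the sentence should say so.

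The cost is one sentence and a check of the script. No new data are needed, because wear minutes must already be derived to apply the 10 h per day rule. The sample size and the secondary outcome definitions need no change on this account.

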#### Secondary outcomes

Other objective measures of physical activity, such as time spent in light and moderate-vigorous physical activity, number of steps and time spent in sedentary behaviour, will be considered secondary outcomes. These data will be collected with the same procedure reported for counts per min. Sedentary time will be defined as values less than 100 count/min, light physical activity will be defined as values between 100 and 2019 counts/min and moderate-vigorous physical activity will be defined as values greater than 2020 counts/min [34]Self-reported physical activity level will be measured with the Baecke Habitual Physical Activity Questionnaire [22]. This questionnaire consists of 16 items covering three dimensions: leisure-time and locomotive physical activities; leisure-time physical exercises; and occupational physical activities. The total score ranges from 3 to 15, with higher scores indicating higher physical activity levelsSelf-reported sedentary behaviour will be measured with questions about the time spent in sedentary behaviour across five different domains in a usual weekday [38]: workplace, commuting, school/university, watching TV, and computer use. Before quantifying the time spent in each sedentary activity, the participants will be asked if they are exposed, or not, to each behaviour. We will use the sum of the domains as well as the time spent in each sedentary behaviourDepression will be assessed with The Center for Epidemiological Studies – Depression (CES-D) scale [39]. The CES-D scale assesses the frequency of depression symptoms in the last week with 20 questions. Total scores range from 0 to 60 and higher scores indicate higher depression levelsQuality of life will be assessed using the EuroQol Visual Analogue Scale (EQ-VAS) [40]. In the EQ-VAS, respondents report their perceived health status with a grade ranging from 0 (the worst possible health status) to 100 (the best health status)The Pain Self-Efficacy Questionnaire (PSEQ) [41] will be used to assess pain self-efficacy. The PSEQ contains 10 items with scores ranging from 0 to 6. Final scores range from 0 to 60 with higher scores indicating more confidence to perform an activity despite the painWeight-related outcomes – Body Mass Index and waist-to-hip circumference will be used to measure weight-related outcomes. Body Mass Index will be calculated based on weight and height measured by a digital scale and an stadiometer and waist and hip circumference using an anthropometric measuring tape. Waist circumference will be measured midway between the 10th rib and the top of the iliac crest and hip circumference as the widest part over the buttocks to the nearest 0.5 cm

At the post-intervention assessment, we will also collect the subjective perception of recovery with the Global Perceived Effect Scale (GPES) [42] that ranges from − 5 to + 5 with higher scores indicating higher recovery from the condition. In addition, the participants will rate the credibility of the treatments using a scale (Appendix 1) consisting of four questions on a 7-point scale with scores ranging from 0 (not confident or not logical) to 6 (absolutely confident or very logical) [30].

### Data analysis

Continuous variables will be reported using mean (standard deviation) or median (interquartile range), depending on the data distribution, and dichotomous and categorical variables will be reported using frequencies (proportion). All data will be analysed following intention-to-treat principles. The difference between groups will be analysed with linear mixed models using fixed effects for group, time and group-versus-time interaction and random intercepts for individuals to account for the dependence of repeated measures. Statistical significance will be set at 0.05. We will report the number of participants with missing scores for each outcome. The statistical software SPSS V.20.0 (IBM corporation, Somers, NY, USA) will be used for data analysis. Planned subgroup analyses will investigate differences in effects of the intervention by physical activity levels at baseline assessment and pain self-efficacy. In addition, we will also conduct secondary analyses to investigate the treatment effects considering the adherence to treatment using a complier average causal effect (CACE) approach.

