**Methods:**

This study will be a two-group, single-blind, randomised controlled trial. One hundred and sixty adults with chronic, nonspecific LBP will be recruited. Participants allocated to both groups will receive a group exercise programme. In addition, the intervention group will receive health coaching sessions (i.e. assisting the participants to achieve their physical activity goals) and an activity monitor (i.e. *Fitbit Flex*). The participants allocated to the control group will receive sham health coaching (i.e. encouraged to talk about their LBP or other problems, but without any therapeutic advice from the physiotherapist) and a sham activity monitor. Outcome measures will be assessed at baseline and at 3, 6 and 12 months post randomisation. The primary outcomes will be physical activity, measured objectively with an accelerometer, as well as pain intensity and disability at 3 months post randomisation. Secondary outcomes will be physical activity, pain intensity and disability at 6 and 12 months post randomisation as well as other self-report measures of physical activity and sedentary behaviour, depression, quality of life, pain self-efficacy and weight-related outcomes at 3, 6, and 12 months post randomisation.

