### Outcomes

The measures will be collected using REDCap (Research Electronic Data Capture) [31] hosted at Sao Paulo State University. Data will be collected and stored in spreadsheets by assessors blinded to group allocation. At baseline assessment, the physiotherapist assessors will collect data on participant characteristics (i.e. age, gender, educational level, presence of comorbidities, medication use and employment status). To characterise the study participants, information on fear of movement measured with the Tampa Scale for Kinesiophobia (TSK) [32] and prognosis risk measured with the Örebro Musculoskeletal Pain Screening Questionnaire (ÖMPSQ) [33] will be collected at baseline. Outcome measures will be assessed at baseline, post intervention (i.e. 3 months after randomisation) and at 6 and 12-month follow-ups. Details on the primary and secondary outcomes are reported below:

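### The mixed model states no baseline covariate or common-baseline constraint, so the 3-month effect is unbiased but less precise than the data already collected allow

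*Protocol article*

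**What the plan says.** The Data analysis section fixes the model terms: "linear mixed models using fixed effects for group, time and group-versus-time interaction and random intercepts for individuals". Baseline appears elsewhere in that section only as a subgroup factor (physical activity at baseline), which concerns effect modification and does not adjust the main comparison.

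The baseline values exist. The Outcomes section states: "Outcome measures will be assessed at baseline, post intervention (i.e. 3 months after randomisation) and at 6 and 12-month follow-ups". The Procedures section places randomisation after the baseline assessment. The abstract sets the primary time point for accelerometer-measured physical activity, "as well as pain intensity and disability at 3 months post randomisation".

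The article does not say whether baseline is one of the levels of time, or which contrast from the model is the 3-month effect.

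For counts per min, the Sample size section plans on a "mean difference between groups of 59.2 counts per min, a standard deviation of 111.6 counts per min". Its power, significance level and allowance for attrition are given under Working below. For pain it assumes a "between-group difference of 1 point (standard deviation (SD) = 1.84) in the numerical pain rating scale". For disability the assumed difference and SD are 4 points and 4.9.

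**The concern.** With group, time and their interaction all unconstrained, the 3-month effect can be read from the model in two ways. If baseline is a level of time and the 3-month interaction term is used, the estimate is the difference between arms in mean change. If the group difference at 3 months is used, the estimate is the raw difference in means and the participant's own baseline plays no part.

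Neither uses baseline efficiently. The change contrast subtracts baseline with a slope of exactly 1, which over-corrects a chance imbalance whenever the correlation is below 1 (equal variances assumed). The unadjusted contrast does not correct it at all. Baseline is measured before randomisation on all three primary outcomes, so adjustment is valid and the data are already in hand.

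At stake is the precision of the primary estimates and, in one part of the plausible range, whether the stated power is reached.

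**Working it through.** **Inputs from the Sample size section.** Counts per min: difference 59.2, SD 111.6, d = 59.2/111.6 = 0.530. Pain: 1/1.84 = 0.543. Disability: 4/4.9 = 0.816. Alpha 0.05, power 0.80, 15% loss, 80 per arm, hence 80 × 0.85 = 68 evaluable per arm.

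**Assumptions.** Two-sided alpha (sidedness is not stated). Rho of 0.3 to 0.7 (none is given). The planning SDs are SDs of the outcome itself; the article does not say so for pain and disability.

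**The plan's own figure.** For counts per min, the normal formula gives n = 2(1.960 + 0.842)²/0.530² = 55.8, so 56 per arm; 56/0.85 = 65.9, so 66 per arm and 132 in total. The t-based version gives 57 per arm; 57/0.85 = 67.1, so 68 per arm and 136 in total. The stated 160 is not reproduced by its inputs. It is larger than they require, which leaves slack here.

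**Variance factors.** With equal variances and correlation rho, the variance of the 3-month contrast is SD² × (2/n) × f:
- change from baseline: f = 2(1-rho)
- unadjusted: f = 1
- baseline-adjusted: f = 1-rho²

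These were checked against the planned model with four time points and 68 per arm. The generalised least squares standard errors equalled the formulas. In one simulated complete data set, the interaction estimate equalled the difference in mean change (43.956 both ways), and the follow-up-only contrast equalled the raw difference in means (56.638 both ways).

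**Excess variance over adjustment.** Change: 2(1-rho)/(1-rho²) = 2/(1+rho), that is 1.54, 1.33 and 1.18 at rho 0.3, 0.5 and 0.7. Unadjusted: 1/(1-rho²), that is 1.10, 1.33 and 1.96. One contrast loses most at low rho and the other at high rho.

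**Standard errors, counts per min, 68 per arm.**

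| rho | change | unadjusted | adjusted |
|---|---|---|---|
| 0.3 | 22.6 | 19.1 | 18.3 |
| 0.5 | 19.1 | 19.1 | 16.6 |
| 0.7 | 14.8 | 19.1 | 13.7 |

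**Power.** Two-sample t test, 68 per arm, effect size d/√f.

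| Outcome | rho | change | unadjusted | adjusted |
|---|---|---|---|---|
| Counts per min | 0.3 | 74% | 87% | 90% |
| | 0.5 | 87% | 87% | 94% |
| | 0.7 | 98% | 87% | 99% |
| Pain | 0.3 | 76% | 88% | 91% |
| | 0.5 | 88% | 88% | 95% |
| | 0.7 | 98% | 88% | 99% |
| Disability | 0.3 | 98% | >99% | >99% |
| | 0.5 and 0.7 | >99% | >99% | >99% |

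Solving for 80% power, the change contrast falls short when rho is below about 0.40 (counts per min) or 0.37 (pain). The normal approximation gives 0.39 and 0.36. The unadjusted contrast does not fall below 80% for any outcome.

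**The case against.** The planned model is legitimate and widely used, and under randomisation both of its readings are unbiased with correct type I error. Preferring baseline adjustment improves the plan; it does not correct an invalid analysis. That stands.

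A reader might infer that the plan ignores baseline altogether. The article does not support this. With baseline among the levels of time, which the assessment schedule makes natural, the interaction contrast does subtract it. At high rho little is then lost: at 0.7 power is 98% against 99%, and at 0.8 the excess variance is 2/1.8 = 1.11.

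The size of the loss rests on a rho that the article does not give. The pain and disability SDs come from a cited earlier trial and could be SDs of follow-up, of change or of residuals. For counts per min the outcome-SD reading is better supported, because the target is expressed as a 20% difference in activity level. These caveats limit the power figures. They do not alter the ordering of the three variance factors.

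Finally, covariates and contrasts are often left to a statistical analysis plan, which is not shown. That weakens the point without removing it: the article lists its fixed effects and baseline is not among them, so adding it changes the stated method.

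**Conclusion.** The point holds as one of precision. As written, the model yields a change or an unadjusted contrast at 3 months, and each is less precise than a baseline-adjusted contrast for any rho strictly between 0 and 1. Over rho 0.3 to 0.7 the excess variance is 54% down to 18% for change and 10% up to 96% for unadjusted.

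It would be tempting to conclude that the trial is biased or underpowered. Neither follows. The stated 80% is at risk only if the change contrast is the test and rho is below about 0.40 for counts per min or 0.37 for pain. Disability keeps about 98% power or more on either reading.

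These figures assume two-sided 5% tests, 68 evaluable per arm, equal variances over time, and planning SDs that are outcome SDs. The equalities are exact for complete data and approximate when visits are missing.

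**What to change.** Choose one of two models and state it:

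- Model the 3-, 6- and 12-month values as the response, with the baseline value of the same outcome and its interaction with time as covariates, alongside group, time and group-by-time.
- Keep baseline in the response as a level of time, and constrain the two arms to a common baseline mean.

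The two are closely related but not identical when baselines are missing. The second retains participants whose baseline accelerometer week fails the wear-time rule (at least 10 hours on at least 5 days). Under a random intercept alone it also assumes one variance and one correlation across all visits, whereas the first lets the baseline slope differ by visit.

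Name the 3-month group contrast from the chosen model as the primary estimate for each primary outcome. The cost is wording only: no extra data or participants, and the planned software can fit it. The choice should be fixed before outcome data are examined by arm.
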